## Abstract

**Background:**

Several studies document disparities in access to care and quality of care for depression for African Americans. Research suggests that patient attitudes and clinician communication behaviors may contribute to these disparities. Evidence links patient-centered care to improvements in mental health outcomes; therefore, quality improvement interventions that enhance this dimension of care are promising strategies to improve treatment and outcomes of depression among African Americans. This paper describes the design of the BRIDGE (Blacks Receiving Interventions for Depression and Gaining Empowerment) Study. The goal of the study is to compare the effectiveness of two interventions for African-American patients with depression--a standard quality improvement program and a patient-centered quality improvement program. The main hypothesis is that patients in the patient-centered group will have a greater reduction in their depression symptoms, higher rates of depression remission, and greater improvements in mental health functioning at six, twelve, and eighteen months than patients in the standard group. The study also examines patient ratings of care and receipt of guideline-concordant treatment for depression.

**Methods/Design:**

A total of 36 primary care clinicians and 132 of their African-American patients with major depressive disorder were recruited into a cluster randomized trial. The study uses intent-to-treat analyses to compare the effectiveness of standard quality improvement interventions (academic detailing about depression guidelines for clinicians and disease-oriented care management for their patients) and patient-centered quality improvement interventions (communication skills training to enhance participatory decision-making for clinicians and care management focused on explanatory models, socio-cultural barriers, and treatment preferences for their patients) for improving outcomes over 12 months of follow-up.

**Discussion:**

The BRIDGE Study includes clinicians and African-American patients in under-resourced community-based practices who have not been well-represented in clinical trials to improve depression care. The patient-centered and culturally targeted approach to depression care is a relatively new one that has not been tested in most previous studies. The study will provide evidence about whether patient-centered accommodations improve quality of care and outcomes to a greater extent than standard quality improvement strategies for African Americans with depression.

**Trial Registration:**

ClinicalTrials.gov NCT00243425

## Background

In the United States, the majority of individuals with mental disorders are untreated or poorly treated, and this is particularly true for ethnic minorities [1,2]. Despite the proven efficacy of pharmacotherapy and psychotherapy for depression, several studies have found that African Americans with depressive disorders receive lower quality of care [3-5]. African Americans are more likely to seek mental health care in primary care settings [6], where disparities in diagnosis [4,7] and appropriate pharmacotherapy and psychotherapy referrals persist [3,4,8,9]. Disparities between African Americans and whites in the adequacy of depression treatment are related to lower rates of initiating treatment with antidepressant medications, and not to disparities in initiating counseling or receiving adequate medications or counseling once initiated[10,11]. Additionally, disparities in depression care are not entirely explained by differences in education, income, and health insurance coverage [5,12,13].

Physician knowledge, attitudes, and skills, patient-physician communication, as well as patient cultural beliefs, attitudes, and preferences, are potential intervention targets to improve outcomes and reduce disparities in depression care. Primary care physicians discuss depression at lower rates and engage in less rapport-building with African-American patients [14]; this could partially explain lower recognition and treatment rates among African-American patients. Compared to white patients, African-American patients express stronger preferences for counseling [15] and spiritual approaches [16], and more negative attitudes toward antidepressant medication [17,18], the most common form of treatment of depression used by primary care physicians.

Although quality improvement (QI) strategies for depression enhance appropriate care and improve clinical outcomes among minorities, some of these interventions are less effective among minorities than whites at improving functional outcomes, and they do not eliminate disparities in depression treatment and clinical outcomes over 12 months [19,20]. The Institute of Medicine includes patient-centeredness--'providing care that is respectful of and responsive to individual patient preferences, needs, and values, and ensuring that patient values guide all clinical decisions'--as an important dimension of healthcare quality [21]. Interventions that focus on patient-centered communication have shown improvements in patient adherence, patient satisfaction, and mental health outcomes [22]. Additionally, interventions that use cultural leveraging increase patients' knowledge, decrease access barriers, and improve providers' cultural competence [23]. However, with a few exceptions [19,24], most QI strategies for depression target provider knowledge of treatment guidelines and disease-oriented collaborative case management of patients, rather than the quality of patient-clinician communication or the cultural acceptability of treatment approaches for patients [25-28]. Improving outcomes for ethnic minority patients with depression beyond those achieved in standard QI interventions may require interventions aimed at improving patient-clinician relationships and making healthcare systems more responsive to patients' needs and preferences.

## Methods

### Study design and specific aims

#### Specific aim one

Recruit 30 primary care clinicians and 250 of their African-American patients with major depressive disorder (MDD) into the Patient-Centered Depression Care for African Americans study. The study has an acronym, 'BRIDGE'--Black Receiving Interventions for Depression and Gaining Empowerment. BRIDGE is a cluster randomized controlled trial with two experimental groups: a standard state-of-the-art depression intervention based on the chronic care model and a patient-centered intervention that supplements standard interventions for depression by tailoring them to individual patients' stated concerns and incorporating patient-centered communication skills and cultural sensitivity training for clinicians (Figure 1).

**Figure 1 F1:**
[figure not shown]
**BRIDGE study design**.

#### Specific aim two

Compare the effectiveness of the patient-centered intervention with the effectiveness of the standard intervention by evaluating their impact on the following patient outcomes at six and 12 months: depression symptom reduction; depression remission; functional status improvement; and receipt of guideline-concordant treatment.

#### Specific aim three

Compare the effectiveness of the patient-centered intervention with the effectiveness of the standard intervention by evaluating their impact on the following processes of care rated by patients at six and 12 months of follow-up: satisfaction with the quality of technical and interpersonal aspects of care in general; satisfaction with depression care in particular, and patients' and clinicians' attitudes regarding care of depression.

Interventions that target providers or patients alone have been insufficient to improve quality of depression care; therefore, it is important to test combined patient and clinician interventions. When interventions that target clinicians are initiated while the effects of the outcomes are measured at the patient level, a traditional randomized trial design with one patient per provider would offer optimal internal validity, but is often not feasible because it requires randomizing a large number of providers. Additionally, although further randomizing patients within each clinician cluster is theoretically possible and offers the added benefit of examining clinician and patient intervention effects separately, it is logistically challenging, resource intensive, and presents the relatively small possibility of cross contamination of the patient intervention among patients within the same clinician cluster. Therefore, for this study, the investigators chose a cluster design in which clinicians and their patients were randomized as one unit.

We hypothesize that compared to patients in the standard intervention group, at follow-up, patients in the patient-centered intervention group will decrease their level of depressive symptoms, remit from depression, improve their functional status, and receive guideline-concordant treatment to a greater extent; give higher ratings of partnership with providers, quality of depression care, and satisfaction; and report more positive attitudes regarding treatment choices for depression.

#### Study populations and settings

The BRIDGE study occurs in urban primary care sites in Baltimore, Maryland and Wilmington and Newark, Delaware. Maryland primary care sites are affiliated with Baltimore Medical System (one site), Baltimore Medical Surgical Associates, an affiliate of Greater Baltimore Medical Center (one site), Johns Hopkins Community Physicians (five sites), and Sinai Hospital, a member of MedStar Health (one site). Delaware primary care sites include two federally-qualified community health centers--Henrietta Johnson Medical Center (one site) and Westside Family Health (one site). These sites were chosen because they are community-based, serve a patient population that is at least 50% African American, include patients with a range of socioeconomic backgrounds, and are interested in improving care for their African-American patients.

### Recruitment strategies

#### Clinicians

Clinicians received an introductory letter that described the study and was co-signed by the medical director of their respective organization and the principal investigator. The letter outlined the goals of the study, gave a general description of the interventions, and described the responsibilities of clinicians caring for study patients. The letter also informed clinicians they would receive continuing medical education (CME) credits; an educational program about depression delivered to them in their office by a primary care physician/psychiatrist team; tailored, individualized feedback regarding their interviewing skills (either during or at the end of the study), and $200 paid to them or their organization. Subsequently, the principal investigator explained the study to prospective clinician participants at regular practice/staff meetings and answered any questions they had. At the conclusion of the presentation, clinicians were given a sign-up form that they could return immediately, fax, or mail to the principal investigator's office. Research staff made follow-up phone calls or visits to sites that had additional questions and to clinicians who did not respond within two weeks of a site presentation. Practice leaders facilitated communication with the clinicians and their staff.

#### Patients

On onsite recruitment days, participating clinics placed signs in registration areas that asked, 'Do you want to improve your emotional health and possibly earn up to $75?' The signs also specified which clinicians were participating in the study. During registration, patients were given a card that informed them their clinician was participating in a study to improve emotional health in African Americans, and they might be approached by a research assistant to ask if they were willing to participate. The patient could return the card to the receptionist if the patient was not African-American and/or did not wish to be approached. Those who agreed to be screened completed the procedures in a private area of the clinic. The research assistant described the study and obtained verbal consent to complete a 10-minute depression screening interview in a private room. Patients who were positive on the first-stage depression screen completed full written study consent, and a research assistant arranged for the patient's medical visit to be audio taped.

Patients who screened positive for depressive symptoms in clinical sites were called at home within two weeks of their onsite screening to complete the second-stage screen (to determine whether they had a diagnosis of MDD by the Composite International Diagnostic Interview, or CIDI) with a 40-minute telephone baseline interview [29,30]. If they met diagnostic criteria, they were randomized according to their clinician's intervention assignment and told to expect a phone call from a depression care manager within a few days; interviewers also obtained respondents' consent to be called for 30-minute follow-up interviews at 6, 12, and 18 months from the baseline interview.

Two other recruitment strategies supplemented the onsite approach. For these patient recruitment approaches, we obtained a waiver of HIPAA privacy authorization from the Johns Hopkins IRB and entered into agreements with the participating health plans to allow data sharing. The second recruitment approach was to have clinical managers at participating primary care sites help identify potential African-American study subjects using administrative and scheduling data. Field research staff then did onsite recruitment and screening at clinics where African-American patients were already scheduled to see a participating provider. The third patient recruitment approach was developed to meet requests from many participating clinicians that the study include some of their patients with known depression. Clinicians were asked to nominate 20 of their known African-American patient cases with MDD for possible inclusion in the study. Clinicians recommended patients with a broad spectrum of depression symptoms and in various stages of care. We sought and obtained IRB approval for clinicians to give research assistants patient contact information (*i.e*., name, address, phone number, and medical record number) for the purpose of preparing a letter that would be signed by the patient's clinician. Information packets containing the clinician's signed letter detailing the study goals and objectives and a prepaid study postcard that offered patients an option to refuse participation were sent to potential participants. Upon receipt of the letter, patients either called the study office, or, if no refusal postcard was received within two weeks of the mailing, they were called by study staff. In either case, during the telephone call patients were told about the study, asked questions to confirm eligibility, and asked if they would be willing to speak further about the study with a member of the study staff when they arrived at their next appointment. If they agreed, a field research assistant met the patient at the clinic prior to their next appointment. The research assistant administered the brief screening questionnaire, and the recruitment process proceeded as described above.

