#### Randomization

Randomization was stratified by study site and conducted at the clinician level with patients sequentially selected within each randomized clinician (10 patients from each clinician). Within each study site (stratum), a randomization schedule was generated through computer by the study statistician using the Moses and Oakford algorithm [32]with the block sizes of two or four randomly created in a four to one ratio. Informed consent and baseline data collection from clinicians (background questionnaire and videotaped interview with the standardized patient) were completed before participating clinicians were randomly assigned (using a blind and secure allocation by computer) to either the standard or the patient-centered intervention. At the screening visit, patients of enrolled clinicians provided oral consent to complete the screening questionnaire. Once eligibility was confirmed, written consent and screening visit data were collected. Additionally, study staff obtained permission from eligible patients to contact them several times over the next 12 months. Patients were then assigned to the standard or patient-centered intervention according to their clinicians' randomization status. The patient recruiters were blinded to the clinicians' randomization assignment during recruitment, and the patients did not know their assigned treatment status until after enrollment. Due to the behavioral nature of the interventions, blinding or masking of study participants, investigators, and depression care managers was not possible. However, interviewers who collected baseline and follow-up data from patients at six and 12 months were masked to clinician and patient intervention assignment.

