### Baseline characteristics of study sample

#### Baseline characteristics of the clinicians

Clinicians were enrolled between June 2004 and March 2006. We contacted 108 clinicians, of whom 72 were excluded; nine clinicians did not respond despite several phone calls, faxes, and emails from the study, and 63 clinicians refused to participate, citing lack of time or interest. Thirty-six clinicians were randomized to either the patient-centered intervention (n = 15) or the standard QI intervention (n = 21); one of these clinicians left the clinical site before baseline data collection and intervention delivery; eight clinicians were unable to contribute patients to the study (three left the site prior to patient recruitment; one went on maternity leave, and three were determined to have an inadequate sample of potentially eligible patients in their panel). (Figure 2) Characteristics of the 36 primary care clinicians recruited to the study are shown in Table 5. They were mostly general internists (58%) with a mean age of 42.4 years and mean practice experience of 6.9 years. Sixty-one percent were women, and they were ethnically diverse (28% African American, 17% Asian, and 47% White).

**Table 5 T5:** BRIDGE Study: Demographic and baseline characteristics for 36 primary care clinicians

Characteristic	No. of PCPs (%)	Mean (standard deviation)
Age, years		42.4 (9.7)
Women	22 (61)	
Ethnicity		
African American	10 (28)	
Asian	6 (17)	
White	17 (47)	
Other	3 (8)	
Experience at current practice, years		6.9 (7.0)
Internal medicine	21 (58)	
Board certified	27 (75)	
CME in the past three years, hours		
Communication		6.2 (11.7)
Depression		5.0 (7.79)
Diversity		5.7 (20.12)
Definitely:		
Need to change way evaluate and manage MDD	3 (8)	
Make an effort to change way evaluate and manage MDD	7 (19)	
Likelihood of first-line treatment		
Very likely:		
Assess but not treatment	1 (3)	
Prescribe medication	18 (50)	
Counsel	6 (17)	
Refer to mental health specialist	14 (39)	
Very confident caring for:		
Socially disadvantaged	16 (44)	
Minority patients	19 (53)	
Very skilled in:		
Diagnosing major depression	9 (25)	
Managing simple antidepressant therapy (one med)	10 (29)	
Providing emotional support	5 (15)	
Following those in remission every six months	9 (25)	

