Limitations of the study should be discussed. The cluster design presents unique challenges with regard to comparability of groups (at the cluster and individual patient level), allocation concealment, maintenance of ITT principles, empty clusters, and participant switches from one cluster to another [55]. Several strategies have been recommended to overcome recruitment challenges: monitoring cluster guardian (*e.g*., practice leader) adherence to the study protocol before randomization of the cluster; including at least one patient participant before randomizing a cluster; and using recruiters who are blinded to participant allocation status. In this study, there was loss to follow-up among randomized clinicians before patient recruitment, which led to empty clusters (*e.g*., clinicians who did not contribute patients to the study) and failure to reach the recruitment target among patients, which may compromise the study's statistical power to detect differences in the primary outcome. Due to the staff resources available for recruitment and time frame needed for delivery of the clinician interventions, it was not feasible to delay randomization of clinicians until the first patient in each cluster was recruited. However, recruiters in this study were blinded to the allocation status of each cluster and its patients. With regard to analysis challenges, empty clusters and patients who switch from one cluster to another may lead to violation of the ITT principle. Recommendations include taking into account both clusters and individuals that withdraw or are lost to follow-up by using *ad hoc *missing data methods; keeping clusters as they were randomized, and using adjustment or propensity-score methods to deal with potential imbalances in both cluster and individual characteristics. In addition to these strategies, we will conduct sensitivity analyses to examine the potential impact of deviation from assumptions underlying such analytic approaches on the robustness of the study findings. Another design constraint is the limited ability to identify which aspects of the multi component interventions are most effective; we intend to conduct *post-hoc *analyses to determine whether the number of intervention contacts, use of intervention materials, and rating of intervention effectiveness by clinicians and patients are related to study outcomes.

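### Nomination of known cases by clinicians who probably knew their arm allows selection by arm, and blinding the recruiters does not prevent it

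*Protocol article*

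**What the plan says.** Under Recruitment strategies (Patients), two approaches rest on waiting-room contact and on clinic scheduling data. A third was "developed to meet requests from many participating clinicians that the study include some of their patients with known depression". For it, "Clinicians were asked to nominate 20 of their known African-American patient cases with MDD for possible inclusion in the study". The article adds that the nominees covered a wide range of symptoms and stages of care, and that the invitation letter carried the clinician's own signature.

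The Randomization section describes allocation by clinician, with "patients sequentially selected within each randomized clinician". On masking, it says that "blinding or masking of study participants, investigators, and depression care managers was not possible", but that recruiters and the interviewers at baseline, six and 12 months were masked.

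The Discussion concedes that "it was not feasible to delay randomization of clinicians until the first patient in each cluster was recruited" and sets against this that "recruiters in this study were blinded to the allocation status of each cluster and its patients".

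The analysis section (Main outcome measures and statistical analysis plan) puts site and clinician characteristics in every model and adjusts for variables found to differ between arms. The Discussion adds adjustment or propensity-score methods and sensitivity analyses. Recruitment route is not named in any of these places, nor in Table 6.

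**The concern.** In a cluster trial, randomising clinicians balances patients in expectation only if entry to the trial does not depend on the arm. If a clinician who knows the arm chooses whom to put forward, the choice can depend on it. A clinician trained in communication skills may think of different patients from one given guideline detailing alone, for example more reluctant, more chronic or more engaged ones. The arms would then differ before treatment starts, in features that affect change in CES-D over 12 months.

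The safeguard that the Discussion relies on concerns the recruiters. In the nomination route they are not the people who make the first selection.

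**Working it through.** There is no stated figure to reproduce. The check is of the order of events, of where each safeguard acts, and of what the planned model can adjust for.

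**1. Were clinicians randomised before nomination?**
- "Clinicians were enrolled between June 2004 and March 2006", and patients were approached between October 2005 and August 2006. The windows overlap from October 2005 to March 2006, so the dates alone do not settle it.
- The Discussion says randomisation could not wait for a cluster's first patient. The clinician baseline section reports randomised clinicians who left before patient recruitment.
- Table 3 lists the audiotapes with depressed patients as post-intervention only, and note 7 of Table 4 ties the enrolment-visit audiotapes to the time after the clinician intervention.
- All of this points to nomination after randomisation. No sentence dates the nominations.

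**2. Did clinicians know their arm?** Masking of participants is said to be impossible. Patients are said not to have known their assignment until after enrolment; nothing similar is said of clinicians. Only the patient-centered arm had the individual CD-ROM communication program (Clinician interventions), although both arms had two detailing visits. Knowledge of the arm at nomination is therefore probable but not stated.

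**3. Where does each safeguard act?**
- Blinded recruiters: after the clinician has named the patient.
- On-site screener and masked telephone CIDI: after nomination. They fix eligibility, but leave prognosis, chronicity and engagement free to vary among eligible patients.
- Adjustment for imbalance: at analysis, and for measured variables only.

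None acts on the choice itself.

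**4. How many patients came by this route?** The patient flow is 1,486 - 613 - 642 = 231, then 231 - 35 - 22 - 42 = 132. It accounts for every enrolled patient under a waiting-room description, with no split by route. Nominees were met at the clinic before an appointment, so they may be among the 1,486. The capacity was large: if 36 - 1 - 8 = 27 clinicians contributed patients, 27 x 20 = 540 nominations were possible against 132 enrolments. At baseline 101 of 132 (76.5%) were taking antidepressants, which fits many known cases but does not show how they were recruited. The share is unknown.

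**5. Scale, on assumed inputs only.** Let p be the nominated share, equal in both arms, and d the difference between arms in the improvement that nominated patients would show under identical care. Then bias = p x d. The yardstick is the 3.6-point difference in Sample size considerations.

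| p (assumed) | d = 1 point (assumed) | d = 4 points (assumed) |
|---|---|---|
| 10% | 0.1 (3% of 3.6) | 0.4 (11%) |
| 25% | 0.25 (7%) | 1.0 (28%) |
| 50% | 0.5 (14%) | 2.0 (56%) |

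The article supports no particular cell, and d may have either sign.

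**6. Would adding route as a covariate help?** The planned mean model is saturated in arm by visit, and the primary contrast is change from baseline to 12 months. With a route main effect, the mean for arm g, visit t and route r is mu(g,t) + b x r. The term b x r is the same at baseline and at 12 months, so it drops out of each patient's change and essentially cancels from the contrast. With a route-by-visit term b(t) x r, the contrast is corrected by [b(12) - b(0)] x (difference between arms in nominated share). That deals with unequal shares. It does not touch d, the difference between arms within the nominated group. Leaving nominated patients out removes the p x d term.

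**The case against.** The strongest reply has four parts.

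- **Timing.** The article never says when a clinician nominated relative to learning the assignment. This stands. A reader might infer that it records nomination by unmasked clinicians; it does not, and the point has to be put as a probability.
- **Analysis.** A reader might infer that the analysis ignores recruitment route. The documents do not support that. Baseline comparability is to be checked, imbalances adjusted for in all ITT models, and propensity-score and sensitivity analyses are foreseen. A journal article may also leave the full covariate list to a longer plan. What can be said is that route is not named and that these methods cover measured imbalance only.
- **Eligibility filter.** Nominees faced the same blinded screening and masked CIDI as everyone else, and patients in specialty mental health care were excluded. This narrows the room for selection, but does not remove it among eligible patients.
- **Wording.** Sequential selection can be read as order of enrolment, the sentence on blinded recruiters is true as written, and the Discussion already names comparability and allocation concealment as challenges of cluster designs. So no sentence is false. Still, the account of selection omits clinician discretion, and the safeguard is offered without saying that it misses this route.

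**Conclusion.** The concern holds in a limited form. Nomination by clinicians in clusters already randomised, who probably knew their arm, is a route for selection by arm that recruiter and interviewer blinding cannot close and that the planned adjustment covers only in part. It rests on one inference, that nominations followed allocation and disclosure; several sections support this and none states it.

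The size and direction of any bias cannot be established. The table above shows scale under assumptions and is not an estimate. A reader might infer a definite bias by assuming a baseline CES-D gap and letting it regress to the mean. The documents do not support that step: nominees were chosen as known cases, not on the trial's baseline score, and a stable difference in chronicity need not regress. Nor is the direction given. Nominating harder-to-treat patients in the patient-centered arm would tend to work against that arm; nominating more engaged ones could favour it.

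**What to change.** 1. Code each patient's recruitment route from the recruitment records. Report counts, baseline CES-D and antidepressant use by arm and route.
2. Run a sensitivity analysis of the 12-month CES-D change contrast restricted to patients not nominated by clinicians. The article shows that between-arm patterns at six and 12 months had been seen by the time follow-up was extended to 18 months, so label this analysis post hoc if it is specified after the 12-month data were seen.
3. If route is also adjusted for, enter it as route-by-visit, and note that this handles only unequal nominated shares between the arms.
4. State when nominations were made relative to each clinician's allocation. Qualify the description of sequential selection in the Randomization section, and say in the Discussion that recruiter blinding does not cover the nomination route.

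The cost is some coding from existing records, one extra analysis and a few sentences. No new patients are needed. The restricted analysis has fewer than 132 patients, so it will be less precise and should be read as a check on the primary result.
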